### Calculation of the sample size

The average proportion of participants in whom IGT progressed to T2D in the Finnish DPS study was 3%/year in the intervention group and 6%/year in the control group (4). The absolute incidence of T2D was 32 cases/1,000 person-years in the intervention group and 78/1,000 person-years in the control group (4). Using the results from the Finnish DPS study and assuming similar rates of incident T2D (6%/year) in the control group, a total of 69 individuals of 300 (our sample size) or 23% will develop diabetes during a 3-year intervention. The corresponding numbers in the intervention groups are 31 of 300 or 10%, indicating a 13% difference in incident T2D between these two groups. If α = 0.05 and β = 0.95, only 60 individuals/group are needed to demonstrate statistically significant difference between the intervention and control groups. Our group-based intervention might be less efficient than individual-based approach in the Finnish DPS study. If the effect of intervention is 6% (about half of the effect of that of the Finnish DPS study), then 267 participants are needed. Assuming around 10% of dropouts in this trial, a sample size of 300/each group has a power of 95% to demonstrate statistically significant reduction in incident T2D in the intervention groups compared with the control groups.

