**ClinicalTrials.gov ID:**

NCT02709057 March 15, 2016

The prevalence of diabetes mellitus will likely increase globally from 463 million individuals in 2019 to 700 million individuals in 2045 (1). This epidemic is mainly attributable to type 2 diabetes mellitus (T2D), which represents about 90–95% of all cases. T2D is a metabolic disorder characterized by chronic hyperglycemia and defects in insulin secretion, insulin action, or both. Genetic and lifestyle/environmental factors as well as their interplay contribute to the pathogenesis of T2D. Genome-wide association studies have identified so far >400 variants for T2D (2, 3). Almost all genetic variants regulate insulin secretion, and only a few of them regulate insulin sensitivity.

Several studies have indicated that lifestyle intervention is effective in the prevention of T2D. The first two of these randomized intervention studies, the Finnish Diabetes Prevention Study (Finnish DPS) and the Diabetes Prevention Program (DPP) from the USA (4, 5), showed that lifestyle intervention lowered the risk of T2D by 58% compared with the control group. In the Finnish DPS study (4), only people with impaired glucose tolerance (IGT) were included, and in the DPP study, people with both impaired fasting glucose (IFG) and IGT were accepted as entry criteria (5). Isolated IFG is a prediabetic condition where only fasting glucose is elevated caused by increased gluconeogenesis. Additionally, beta cell function is impaired, and glucagon secretion is inappropriately elevated (6). In contrast, people with combined IFG and IGT have a combination of increased gluconeogenesis, lack of suppression of glycogenolysis by insulin, impaired glucose disposal with extrahepatic insulin resistance, and impaired insulin secretion (7).

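### The sample-size section mixes two incompatible control rates (23% over 3 years is labelled 6%/year, which gives 16.5–18%) and carries them over unadjusted from an all-IGT trial to both genetic-risk strata

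*Protocol article*

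**What the plan says.** All the figures stand in the protocol article under Calculation of the sample size. Two pairs of rates are cited from the Finnish Diabetes Prevention Study. The first is a yearly progression of 3% (intervention) and 6% (control). The second is an incidence of "32 cases/1,000 person-years in the intervention group and 78/1,000 person-years in the control group".

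The planning step then reads: "assuming similar rates of incident T2D (6%/year) in the control group, a total of 69 individuals of 300 (our sample size) or 23" per cent over the 3-year intervention. For the treated arm: "The corresponding numbers in the intervention groups are 31 of 300 or 10%, indicating a 13% difference".

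Two sample sizes follow. For the full effect: "If α = 0.05 and β = 0.95, only 60 individuals/group are needed". For a weaker group-based intervention: "If the effect of intervention is 6% (about half of the effect of that of the Finnish DPS study), then 267 participants are needed". After allowing for about 10% dropout, the section claims 95% power with 300 per group.

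On the source population, the introductory text says: "In the Finnish DPS study (4), only people with impaired glucose tolerance (IGT) were included". Under Participants, this trial admits people with impaired fasting glucose (IFG) with or without IGT, and excludes isolated IGT. Table 2 gives a baseline 2-h glucose of 6.3±1.6 mmol/l in the intervention group. Under Statistical analyses, the intervention is compared with control within the low and the high GRS groups.

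**The concern.** The sentence that sets the expected control events contradicts itself: the stated rate does not yield the stated count. The control risk fixes how many events each stratum will supply. The difference between the two arms' risks is also the benchmark against which the 6-point scenario is called about half of the source effect.

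The rate is borrowed as well. It comes from a population defined by IGT and is applied without adjustment to a population defined by IFG. It is applied identically to low and high GRS, although the score was chosen to separate people by diabetes risk. The primary comparison is made within each stratum, so expected events per stratum decide how a null result in either one can be read.

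**Working it through.** **Inputs.** Control 6%/year or 78/1,000 person-years; intervention 3%/year or 32/1,000; 3 years; 300 per group; 10% dropout, so 270 analysed; α = 0.05. The stated β = 0.95 is read as 95% power. Sidedness is not stated and is taken as two-sided.

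**Step 1: does 6%/year give 69 of 300?**

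| Rate | r × 3 | 1 − (1 − r)³ | 1 − exp(−3r) |
|---|---|---|---|
| Control 6%/year | 18.0% (54) | 16.9% (50.8) | 16.5% (49.4) |
| Control 78/1,000 | 23.4% (70.2) | – | 20.9% (62.6) |
| Intervention 3%/year | 9.0% (27) | 8.7% (26.2) | 8.6% (25.8) |
| Intervention 32/1,000 | 9.6% (28.8) | – | 9.2% (27.5) |

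In brackets: expected cases per 300. No conversion of 6%/year reaches 69; the gap is 15 to 20 cases. The 69 lies next to 70.2, the person-time rate multiplied by 3 without removing cases from the risk set. The stated 31 matches neither intervention rate exactly, but it is only 2 to 4 cases from the person-time figures.

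**Step 2: effect on the benchmark.** With the person-time rates converted to risks, the source effect is 20.9 − 9.2 = 11.7 points, and 6 points is about half of it (6/11.7 = 51%). With the annual rates it is 18 − 9 = 9 points, and 6 points is two thirds of it.

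**Step 3: power with 270 per group**, pooled-variance test of two proportions:

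power = Φ{[d√n − 1.96√(2p̄(1 − p̄))] / √(p₁(1 − p₁) + p₂(1 − p₂))}

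| Scenario | Control vs intervention | Power |
|---|---|---|
| Full effect, as written | 23% vs 10% | 98% |
| Full effect, person-time rates as risks | 20.9% vs 9.2% | 97% |
| Full effect, annual rates, simple | 18% vs 9% | 87% |
| Full effect, annual rates, compounded | 16.9% vs 8.7% | 82% |
| 6 points | 23% vs 17% | 41% |
| 6 points | 20.9% vs 14.9% | 44% |
| 6 points | 18% vs 12% | 50% |

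For example, 18% vs 9%: (0.09 × 16.43 − 1.96 × 0.483)/0.479 = 1.11, and Φ(1.11) = 0.87.

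**Step 4: where 60 and 267 come from.** At 95% power, 23% vs 10% needs 209 per group and 23% vs 17% needs 1,153. The stated figures match the margin-of-error formula for a single proportion, 1.96² × 0.25/d². With d = 0.06 it gives 266.8, so 267. With d = 38/300 (69 − 31 = 38) it gives 59.9, so 60. That formula has no power term. The control rate enters the 60 only through the difference d, and does not enter the 267 at all.

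**Step 5: direction of the rate effect.** At a fixed 6-point difference, a lower control risk raises power (41% to 50%). At a fixed relative effect it lowers power. With the ratio 31/69 = 0.449, power goes from 98% at 23% to 93% at 18%. With half that relative reduction (ratio 0.725), it goes from 45% to 36%.

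**Step 6: population.** The IGT threshold is 7.8 mmol/l: (7.8 − 6.3)/1.6 = 0.94 SD above the mean. Under a normal distribution about 17% lie at or above it. Without that assumption, the mean and SD bound the share only at 53% (Cantelli: 1/(1 + 0.9375²)). Either way, the sample cannot be all IGT.

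**The case against.** The strongest reply is that 23% is not baseless. The sentence just before gives 78/1,000 person-years, and three times that is 23.4%. On this reading the defect is a wrong label. That stands in part: the documents do not show which rate was intended, so a reader who concludes that the true planning value is 17–18% goes too far. The two rates still cannot both describe the control group, and the choice matters for the full effect: 97% power on one, 82–87% on the other.

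Second, a reader might infer that an inflated control rate makes every power figure too favourable. The documents do not support that. The case that supports 300 per group is an absolute 6-point difference, for which a lower control rate helps. Its shortfall from 95% comes from a sample-size formula without a power term and would remain if the rate were corrected.

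Third, the article gives no progression rate for isolated IFG and no count of participants with IGT. The 17% is a normal approximation in the intervention group only. Participants also enter near the fasting threshold, and the outcome counts fasting glucose, HbA1c and drug treatment as well as 2-h glucose. The mismatch of populations is certain from the text, but the size and direction of any bias in the rate cannot be computed.

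Fourth, one might infer that the low-GRS stratum suffers most. No figure supports this, and the Abstract says the two risk groups were matched on fasting glucose, age and body mass index, which may narrow the risk gap.

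**Conclusion.** The point holds as an internal inconsistency together with an unadjusted transfer of rates. The stated 69/300 exceeds what 6%/year yields (49–54) by 15–20 cases; it fits the person-time rate times 3. The source trial was all IGT, this trial is not, and one rate serves both GRS strata without justification.

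With 270 per group and a two-sided 5% test, 95% power is met for the full source effect on the person-time rates. It is missed on the annual rates (82–87%). For the 6-point effect it is missed at each control risk checked from 18% to 23% (41–50%). That last failure is a separate matter of the formula and should not be attributed to the control rate; a lower control rate costs power only if the effect is taken as relative.

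These results assume that β = 0.95 means power, a two-sided test, equal groups, and a comparison of 3-year proportions as the section itself frames it.

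**What to change.** State one source rate, name its type (annual proportion or person-time incidence), and convert it once to a 3-year risk for both arms. Correct the 69, the 31 and the 13-point difference to match, and say whether the reduced effect is absolute or relative.

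Then restate expected events and power separately for GRS quintiles 1–2 and 4–5. Preferably use the observed 3-year incidence in men of the METSIM cohort who meet the entry criteria. The article does not say whether the cohort can supply this. If it cannot, give a stated range of control risks and explain why a rate from an IGT population is being used. Report the number of participants with and without IGT at baseline, so that the comparison with the source trial does not rest on a mean and SD.

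Recruitment closed in April 2018, so this changes text and adds a tabulation, not the design. The cost is that the stated power becomes less favourable; the gain is a sound basis for reading a null result in either stratum.

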**Fig. 1 F0001:**
[figure not shown]
Study design of the T2D-GENE trial. Participants in the intervention and control groups of the trial are divided into two groups based on the genetic risk score for type 2 diabetes (low genetic risk and high genetic risk). IFG, impaired fasting glucose; IGT, impaired glucose tolerance. The duration of the intervention is follow-up time is 3 years for all participants.

For both intervention groups (low GRS and high GRS), control groups of 300 participants (altogether 600 participants) of the METSIM study were selected and matched for GRS, fasting plasma glucose concentration, age, and BMI (Fig. 1). The rationale for these two control groups is to compare the incidence of T2D during the intervention between the two intervention groups and the two control groups.

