### Statistical analyses

The primary analyses for the outcomes (incident T2D) in the time-to-event analyses will be based on a Cox proportional-hazards model with the study group (intervention and control) as a covariate in the low and high GRS groups. Linear regression will be used to evaluate the effect of intervention on insulin sensitivity, insulin secretion, the glucose AUC, and other continuous variables. Comparison between the study groups at baseline and at the end of 3-year intervention will be carried out with t-test (continuous variables) intervention and chi-square test (non-continuous variables).

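### The sample sizes of 60 and 267 for 95% power do not follow from the stated rates; at the planned 6-point effect, 300 per group gives about 41% power per genetic-risk stratum

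*Protocol article*

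**What the plan says.** All the planning figures are in the section on calculation of the sample size.

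- Control risk: "a total of 69 individuals of 300 (our sample size) or 23% will develop diabetes during a 3-year intervention".
- Intervention risk under the full Finnish DPS effect: "The corresponding numbers in the intervention groups are 31 of 300 or 10%, indicating a 13% difference in incident T2D between these two groups".
- Sample size for that effect: "If α = 0.05 and β = 0.95, only 60 individuals/group are needed".
- The article then allows for a weaker, group-based programme: "If the effect of intervention is 6% (about half of the effect of that of the Finnish DPS study), then 267 participants are needed".
- Closing claim, after allowing for about 10% dropout: "a sample size of 300/each group has a power of 95% to demonstrate statistically significant reduction in incident T2D".

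Two other places set the level of the comparison. The text with Fig. 1 gives each GRS group its own controls: "For both intervention groups (low GRS and high GRS), control groups of 300 participants (altogether 600 participants"). The Statistical analyses section specifies a "Cox proportional-hazards model with the study group (intervention and control) as a covariate in the low and high GRS groups". The comparison that 300 per group supports is therefore intervention against control within one GRS stratum.

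**The concern.** Halving a difference in proportions should roughly quadruple the sample size or more. The step from 60 to 267 has that shape, but both numbers are far too small for 95% power at these event rates. The choice of 300 rests on the second one: 267 / 0.90 = 297, rounded to 300.

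The 6-point effect is the scenario the article itself uses to justify 300, and the Discussion names insufficient efficacy of the group-based programme as the study's main challenge. The conclusions the article anticipates depend on whether the intervention works at low and at high genetic risk. If power per stratum is well below 95%, a real benefit can easily show in one stratum and not in the other by chance. Read against a stated 95%, that pattern would look like evidence that genetic risk modifies the effect.

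**Working it through.** **Inputs.** Control risk 23%; intervention risk 10% (full effect) or 23% − 6 points = 17% (reduced effect); alpha 0.05; 300 per group less 10% = 270 evaluable. The article writes beta = 0.95, but its closing sentence shows that power 0.95 is meant. Sidedness is not stated; two-sided is assumed first.

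**Trying to reproduce 60 and 267.** Pooled, unpooled, arcsine, continuity-corrected and log-rank formulas were tried, one- and two-sided, per group and as totals. At the stated 23% control risk, no two-group comparison with 95% power gives either number. Both do come out of the precision formula for a single proportion at p = 0.5, n = 1.96² × 0.25 / d²:

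- d = 0.06: 0.9604 / 0.0036 = 266.8, so 267
- d = 38/300 = 0.1267 (from 69 − 31 = 38 cases): 0.9604 / 0.01604 = 59.9, so 60

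That formula sets a 95% confidence half-width. It has no second group and no power term. That it is the source is inferred from the match, and the finding does not depend on it.

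**Two-proportion sample size**, with p̄ the mean of the two risks:

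n = [1.960·√(2p̄(1−p̄)) + 1.645·√(p1(1−p1) + p2(1−p2))]² / (p1 − p2)²

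- 23% vs 10%: (1.960 × 0.5249 + 1.645 × 0.5168)² / 0.0169 = 208.9, so **209 per group** (about 222 with 69/300 vs 31/300)
- 23% vs 17%: (1.960 × 0.5657 + 1.645 × 0.5641)² / 0.0036 = 1,152.1, so **1,153 per group**, or 1,282 after allowing for 10% dropout
- 23% vs 17% at 80% power: 697 per group
- One-sided at 95% power: 174 and 960 per group

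**Power**, Φ{[(p1 − p2)√n − 1.960·√(2p̄(1−p̄))] / √(p1(1−p1) + p2(1−p2))}. For 23% vs 17% at n = 270: Φ[(0.9859 − 1.1087) / 0.5641] = Φ(−0.218) = 0.414.

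| Comparison | n per group | Power (two-sided) |
|---|---|---|
| 23% vs 10% | 60 | 48% |
| 23% vs 10% | 270 | 98% |
| 23% vs 17% | 267 | 41% |
| 23% vs 17% | 270 | 41% |
| 23% vs 17% | 300 | 45% |
| 23% vs 17%, strata pooled | 540 | 69% |
| 23% vs 15.4% | 270 | 61% |

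The last row applies the risk ratio of 0.67 that the Discussion cites for group counselling (0.67 × 23% = 15.4%). With 270 per group, the smallest drop from 23% detectable with 95% power is about 11.6 points.

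**Cox version (Schoenfeld).** HR = ln(0.83) / ln(0.77) = 0.713. Events needed: 4 × (1.960 + 1.645)² / (ln 0.713)² = 454. Events expected: 270 × (0.23 + 0.17) = 108. Power: 42%.

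**The case against.** The 41% rests on three readings that the article does not spell out: a two-sided test, a control risk of 23% carried into the reduced-effect scenario, and 267 meant per group. The control risk is itself uncertain. The section quotes 6% per year, which over three years gives 17% to 18% (1 − 0.94³ = 16.9%; 3 × 6% = 18%). The 23% instead fits 78 per 1,000 person-years (3 × 7.8% = 23.4%). At 270 per group, two-sided, power for a 6-point drop is 50% from 18%, about 54% from 16% and 68% from 12%. A one-sided test at 23% vs 17% gives 54%. So missing the effect is more likely than not only on some of these readings.

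This stands as a reason to label the replacement figures by their assumptions. It does not rescue the claim. At 18% vs 12%, 95% power still needs 918 per group, and pooling the strata at 23% vs 17% reaches only 69% two-sided or about 79% one-sided. Passing 95% at 540 per arm takes pooling, a one-sided test and a control risk of 12% all at once, which is about half the rate the article states.

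Three further points are fair. The full Finnish DPS effect is well covered, so the wrong figure of 60 did no harm to the design. Controls are matched on GRS, fasting glucose, age and BMI, which might help precision, but no correlation is given and no gain can be credited. The Time table reports 635 recruited; even 317 per group with no dropout would give only about 47%.

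**Conclusion.** The concern holds. Neither 60 nor 267 follows from the stated rates at 95% power; the correct figures are 209 and 1,153 per group, so the article understates the requirement by factors of about 3.5 and 4.3. The closing power claim fails for the effect it was meant to cover: about 41% per GRS stratum and 69% pooled, given 23% vs 17%, a two-sided 0.05 test and 270 evaluable per group. Over control risks from 12% to 23%, per-stratum power is about 41% to 68% two-sided. The claim is sound only for effects of about 11.6 points or more from 23%, which includes the full 13-point Finnish DPS effect (98%). This is the only power statement in the article, so it must be corrected.

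**What to change.** In the section on calculation of the sample size:

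1. Replace 60 by 209 and 267 by 1,153, both per group, and write power = 0.95 (beta = 0.05). State that the test is two-sided.
2. State the control risk the figures rest on, and reconcile 6% per year with 23% over three years. If the lower rate was intended, recompute; 18% vs 12% would need 918 per group.
3. Replace the closing claim by what 300 per group (270 after dropout) delivers at a 23% control risk: about 98% power for 23% vs 10%; about 41% per GRS stratum for 23% vs 17%; about 69% for that effect in a GRS-stratified pooled analysis; and a smallest difference detectable with 95% power of about 11.6 points.
4. Add that a non-significant result within one stratum is not evidence of no effect there.

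Recruitment was completed in April 2018, so this corrects text and interpretation and adds no participants. The cost is that the stated power becomes less favourable.

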## Methods

### Study visits

Participants in the intervention groups have four laboratory visits (0, 1, 2, and 3 years), and participants in the control groups have two laboratory visits (0 and 3 years) (Fig. 2). The study visits at 0 and 3 years include a questionnaire on physical activity at work and leisure time, smoking, alcohol use, history of diseases, and current medication, and dietary habits (food frequency questionnaire), blood pressure (three measurements 1 min apart), body weight, height, and bioimpedance for measure fat percentage. Laboratory measurements include an OGTT (plasma glucose and insulin concentrations at 0, 30, and 120 min), HbA1c, and concentrations of total LDL and HDL cholesterol, total triglycerides, alanine aminotransferase, creatinine, interleukin 1 receptor antagonist, and high sensitivity C-reactive protein. The three-factor eating questionnaire R18 (TFEQ-R18) (12) is used for the evaluation of participants’ eating behavior (cognitive restraint, uncontrolled eating, and emotional eating) during the intervention. In the intervention group, the 1-year visit includes measurement of non-fasting HbA1c. At the 2-year visit, the TFEQ-R18 questionnaire is filled, and body weight, blood pressure, and the laboratory measurements are performed similarly as at 0-year and 3-year visits.

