**Fig. 2 F0002:**
[figure not shown]
Intervention program. The participants belonging to the intervention group have seven group visits (group sessions on motivation; healthy dietary pattern and exercise; weight loss for those whose BMI was >28 kg/m^2^; and group sessions for all at 0, 1, 2, and 3 years for personal feedback from food records). Control groups have laboratory visits at 0 and 3 years, without any group sessions). FR, food record; FFQ, food frequency questionnaire; OGTT, an oral glucose tolerance test.

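### Diabetes is tested for at years 1, 2 and 3 in the intervention groups but only at year 3 in the controls, so the primary Cox hazard ratio partly reflects the visit schedule

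*Protocol article*

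**What the plan says.** All references are to the protocol article.

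- **Schedule (Study visits).** Intervention participants have "four laboratory visits (0, 1, 2, and 3 years), and participants in the control groups have two laboratory visits (0 and 3 years". The Fig. 2 legend agrees: "Control groups have laboratory visits at 0 and 3 years, without any group sessions".
- **Interim tests (Study visits).** "In the intervention group, the 1-year visit includes measurement of non-fasting HbA1c". At year 2, "the laboratory measurements are performed similarly as at 0-year and 3-year visits", which brings in the OGTT and HbA1c.
- **Outcome (Introduction).** A participant becomes a case by fasting glucose, by 2-h glucose, by HbA1c, or by starting drug treatment for T2D within the 3 years. Any one of these is enough.
- **Primary analysis (Statistical analyses).** The "time-to-event analyses will be based on a Cox proportional-hazards model with the study group (intervention and control) as a covariate", fitted in the low and high GRS groups. The same section also plans t-tests and chi-square tests between study groups at baseline and at the end of the 3 years.

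**The concern.** A Cox model compares the arms at each event time, and it needs event times that mean the same thing in both arms. Here they do not.

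1. **Timing.** Intervention cases can be recorded at years 1 and 2. Before year 3 a control can become a case only by starting drug treatment. Equal disease rates would therefore produce earlier recorded events in the intervention arm.
2. **Extra chances.** A man above a threshold at year 2 and below all of them at year 3 is a case in the intervention arm and a non-case among controls.

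Neither effect shrinks with sample size. The hypothesis is that the programme works at both levels of genetic risk, and the Discussion names insufficient efficacy of the group-based format as the main risk. A bias towards no effect could produce that conclusion falsely.

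**Working it through.** **Inputs.** Calculation of the sample size gives 3-year incidences of 23% (69/300) in controls and 10% in the intervention group, and a weaker effect of 6 points, read here as 23% vs 17%. The 23% follows from the quoted 78 per 1,000 person-years: 3 × 0.078 = 0.234. The article also ties it to 6% per year, which gives only 1 − 0.94³ = 16.9%, so 18% was tried as well. The article states no figure for the schedule effect.

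**Assumptions.** Constant hazards; visits exactly at years 1, 2 and 3; no early control cases; year-1 HbA1c finds 30% of those who have become diabetic (values from 0 to 100% give the same hazard ratio); Efron handling of ties.

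**True hazard ratios.** HR = ln(1 − p_I)/ln(1 − p_C). For 17% vs 23%: 0.1863/0.2614 = 0.713. For 10% vs 23%: 0.1054/0.2614 = 0.403.

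**Expected recorded cases per 300**

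| Scenario | Intervention, year 1 / 2 / 3 | Control, year 3 |
|---|---|---|
| 23% vs 23% | 7.5 / 40.5 / 21.0 | 69 |
| 23% vs 17% | 5.4 / 29.6 / 16.0 | 69 |
| 23% vs 10% | 3.1 / 17.2 / 9.7 | 69 |

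**Hand check under no effect.** The score at HR = 1 is the sum over visits of d_I − d·p. Here d_I is intervention cases, d is all cases, and p is the intervention share of the risk set, taken midway through the ties (proportions of one arm).

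- Year 1: 0.0250 × (1 − 0.497) = +0.0126
- Year 2: 0.1349 × (1 − 0.476) = +0.0707
- Year 3: 0.0701 − 0.3001 × 0.4763 = −0.0728

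The sum is +0.0105, where equal schedules give 0. The information, Σ d·p(1 − p), is 0.1148. One step gives ln HR ≈ 0.0105/0.1148 = 0.091, or HR ≈ 1.095. The full solution is 1.094.

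**Solved hazard ratios (Efron)**

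| True HR | Both arms at year 3 only | Planned schedule, timing alone | + 2 points | + 4 points |
|---|---|---|---|---|
| 1.00 | 1.00 | 1.09 | 1.21 | 1.34 |
| 0.713 | 0.714 | 0.77 | 0.88 | 0.99 |
| 0.403 | 0.404 | 0.425 | 0.52 | 0.62 |

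The last two columns add intervention participants who are positive at year 2 but would be negative at year 3. The 2 and 4 points are assumptions; no figure in the article supports a value.

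**Variations under no effect.**
- Control incidence of 18%: 1.07.
- 20–40% of control cases surfacing early through drug treatment: 1.09–1.11.
- Year-3 visits scattered late in both arms (assumed SD 0.1 year): about 1.16.
- Only intervention visits late, same scatter: 0.75.
- Only control visits late: the estimate diverges against the intervention, because control cases then fall after the intervention arm has left the risk set.

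**Error rates (simulation, timing alone).** At 270 per group and true HR 0.713, power is about 40% with common year-3 assessment and about 25–29% under the planned schedule. At 270 per group and 23% vs 10%, it is still about 97%. At 300 per group with no effect, significance against the intervention occurs in about 8% of trials (nominal 2.5%).

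**The case against.** - **Tie handling.** The article names no method. Breslow ties give 1.13, 0.81 and 0.46 in place of 1.09, 0.77 and 0.425, and a reader might take those as the size of the problem. They are not: with both arms assessed only at year 3, Breslow already turns 0.713 into 0.739. The Efron figures isolate the schedule effect. This stands.
- **Main planning effect.** At 23% vs 10%, timing alone would not change the conclusion. This stands.
- **Transient positives.** A reader might infer that a real effect would be wiped out. That needs about 4 assumed points, and the article gives no basis for any value.
- **Direction.** A reader might infer that the bias always runs against the intervention. It does so only if year-3 visits are timed alike. Time table reports recruitment complete in April 2018 and last visits in September 2021, so exact 3-year timing cannot be taken for granted.
- **GRS contrast.** Both GRS groups share the same pair of schedules. Timing inflation runs from about 1.05 (0.425/0.403) to 1.09, so it largely cancels in a ratio of hazard ratios. This stands for timing, but the within-group hazard ratios are the stated primary analysis.
- **A common comparison already exists.** The end-of-trial chi-square is planned, but the Cox model is what the article makes primary, so the chi-square does not repair it.
- **Condensed article.** Confirmation and dating of interim positives may be set out elsewhere. That one interim positive counts as an event is inferred from the outcome definition. The unequal schedule and the choice of model are stated outright.

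**Conclusion.** The concern holds and should be corrected before analysis. Followed as written, the plan yields a hazard ratio that mixes the effect of the intervention with the effect of unequal testing.

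The timing part is modest: an inflation of about 5–9% in the hazard ratio, given constant hazards, 23% control incidence, Efron ties and like-timed visits. It matters most for the weaker effect the article itself plans for, where power drops from about 40% to about 25–29%. The part due to extra detection is in the same direction, but its size cannot be fixed from the document. With unequal year-3 visit timing, the direction is open. The document supports neither a claim of certain bias against the intervention nor a claim that a large effect would be missed.

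**What to change.** Within each GRS group, make the primary comparison T2D status over the common 0–3-year interval: positive at the 3-year OGTT or HbA1c, or drug treatment for T2D recorded by the 3-year visit. Analyse it with a binomial model with complementary log-log link, so that the group coefficient is a log hazard ratio, and use the log of the actual interval between the two visits as offset. Use year-1 and year-2 results for description within the intervention groups. Keep the Cox model counting all detections, with Efron ties, as a sensitivity analysis.

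An interval-censored model alone would not be enough: it corrects the timing but not the extra chances of detection.

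**Cost.** Analysis wording only, since the 3-year tests and the medication questionnaire are already scheduled in both arms. Three downsides should be stated:
- intermediate event dates are not used;
- untreated interim positives who revert are not counted;
- drug treatment prompted by year-1 or year-2 tests leaves some difference in detection.

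Examine the last with a sensitivity analysis on year-3 laboratory status alone, and report drug-start cases by arm.
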